#### **7.4. Compliance with interventions**

Both interventions are automated and centrally delivered linked to the HIC recruitment tracker, so fidelity of delivery is not an issue. Engagement with the interventions (SMS received from participants; Game of Stones website access data, self-report items in questionnaire at 12M), retention and any reasons offered for drop-out will be documented.

## 8. ADVERSE EVENTS

### 8.1. Standard definitions

**Table 2: Definitions of adverse events**

| Term                               | Definition                                                                                                                                                                                                                                                                                                                                                                                                                                                                                                                                                                                                                                                                       |
|------------------------------------|----------------------------------------------------------------------------------------------------------------------------------------------------------------------------------------------------------------------------------------------------------------------------------------------------------------------------------------------------------------------------------------------------------------------------------------------------------------------------------------------------------------------------------------------------------------------------------------------------------------------------------------------------------------------------------|
| Adverse Event (AE)          | Any untoward occurrence in a participant to whom the intervention has been administered, including occurrences which are not necessarily caused by or related to the event.                                                                                                                                                                                                                                                                                                                                                                                                                                                                                                      |
| Serious Adverse Event (SAE) | 
A serious adverse event is any untoward occurrence that:
 

• results in death

• is life-threatening

• requires inpatient hospitalisation or prolongation of existing hospitalisation

• results in persistent or significant disability/incapacity

• is otherwise considered medically significant by the investigator

 
NOTE: The term "life-threatening" in the definition of "serious" refers to an event in which the participant was at risk of death at the time of the event; it does not refer to an event which hypothetically might have caused death if it were more severe.
 |

### 8.2. Operational definitions for this study

In this trial:

- An adverse event is defined as any injury or newly diagnosed health condition (e.g. diabetes mellitus, cancer, etc) that occurred while a man was participating in Game of Stones, in any of the groups, whether or not this was related to his participation in Game of Stones.
- AEs will be recorded by Fieldworkers within the CRF from the time a participant consents to join the study until the end of the 24-month follow-up period.
- Hospitalisations for treatment planned prior to randomisation and routine hospitalisation for elective treatment will **not** be considered or recorded or reported as an AE or an SAE. Complications occurring during such hospitalisation will also not be considered, recorded or reported as an AE or an SAE.
- Any death that occurs during the trial is very unlikely to be related, but all deaths will be documented as AE and relatedness determined.

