### **8.3. Detecting AEs and SAEs**

At each contact with a participant (3, 6, 12 and 24M), the Fieldworker will ask about the occurrence of AEs/SAEs. Open-ended and non-leading verbal questioning of the participant will be used to enquire about AE/SAE occurrence. If any AE is likely to meet the criteria for an SAE, as much detail as possible about the event will be sought from the participant. This a community-based study, and the Fieldworker and PI will not have access to hospital or GP medical records, so the only source of information about the event is likely to be from the participant themselves. AEs/SAEs will be recorded, evaluated, reviewed and reported as described below.

In addition, the research team may be alerted to a possible AE/SAE via screening of text message responses (see Section 8.8 on Safeguarding), or by direct contact with the trial office. If the AE/SAE is confirmed, this will be recorded, evaluated, reviewed and reported as described below.

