## Assessment of Expectedness

If the event has been assessed as being related to the administration of any of the research procedures or to the man's effort to lose weight, an assessment of expectedness is required. The following events are expected:

- Musculoskeletal injuries or musculoskeletal pain
- Cardiovascular events (such as angina, myocardial infarction, palpitations, etc)
- Nutritional deficiencies
- Gall stones, newly manifest or worsening of known symptoms
- Changes in bowel habits
- Negative impacts on mental health (such as depression, fatigue, suicidal thoughts, etc)
- Low blood sugar, changes in diabetic medication, diabetic complications

All other events are considered unexpected.

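### The working adverse event definition in 8.2 conflicts with Table 2 and with the protocol's own list of expected events, so capture of non-serious symptoms and of worsening known conditions is undefined

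*Protocol*

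**What the plan says.** Three parts of protocol section 8 bear on what counts as an adverse event (AE).

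- **8.1, Table 2 (standard definitions).** An AE is "Any untoward occurrence in a participant to whom the intervention has been administered", whether or not it is related. The serious category is equally open: "A serious adverse event is any untoward occurrence that" meets one of the listed seriousness criteria.
- **8.2 (operational definitions).** Under a lead-in that restricts it to this trial: "An adverse event is defined as any injury or newly diagnosed health condition (e.g. diabetes mellitus, cancer, etc"). It applies in every group and regardless of relatedness. The section adds separately that all deaths are to be documented as AEs. It excludes hospitalisation planned before randomisation, routine elective hospitalisation, and complications arising during either.
- **8.4, Assessment of Expectedness.** Events assessed as related are then classed as expected or not. The expected list includes "Low blood sugar, changes in diabetic medication, diabetic complications", "Gall stones, newly manifest or worsening of known symptoms" and "Changes in bowel habits", together with musculoskeletal pain, palpitations, fatigue and suicidal thoughts.

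On recording, 8.2 states: "AEs will be recorded by Fieldworkers within the CRF from the time a participant consents to join the study". Section 8.3 asks for detail on serious events in these terms: "If any AE is likely to meet the criteria for an SAE".

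**The concern.** An expectedness list is of use only for events that have already been recorded and assessed as related. If the definition that decides what is recorded leaves out some of the events on that list, the two parts cannot both be followed.

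What is at stake is the completeness of the safety record. The Trial Summary names adverse events among the 12-month outcomes, and Table 1 lists them at 12 and 24 months. Under 8.5, non-serious AEs reach the PMG and TSC by being collated from what was recorded. Section 8.3 says that staff have no access to hospital or GP records and that the participant is likely to be the only source, so an event not written down at the contact may not be recoverable. The same complaint could also be handled differently depending on whether a Fieldworker works from 8.1, 8.2 or the 8.4 list.

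**Working it through.** No arithmetic applies beyond a count. The check sets each category of the 8.4 list against the two definitions. All of the entries fall under Table 2, because each is an untoward occurrence. The question is which of them also fall under 8.2.

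| Category in the 8.4 list | Fits 8.2 (injury or new diagnosis) | Need not fit 8.2 |
|---|---|---|
| Musculoskeletal | Injury | Pain without injury or diagnosis |
| Cardiovascular | First myocardial infarction | Palpitations without a diagnosis; recurrence of known angina |
| Nutritional deficiency | Newly diagnosed deficiency | None named |
| Gall stones | First presentation | Worsening of symptoms already known |
| Bowel habit | None as listed | The whole entry, a symptom |
| Mental health | Newly diagnosed depression | Fatigue; suicidal thoughts; worsening of known depression |
| Diabetes-related | A newly diagnosed complication, arguably | Low blood sugar or changed medication in a man with known diabetes |

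Six of the seven categories have at least one component outside 8.2, and one category lies outside it entirely.

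The next question is which definition governs.

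1. Section 8.1 is headed as standard and 8.2 as operational for this study. A Fieldworker would naturally follow the second.
2. Section 8.2 adds deaths as a separate bullet. Under Table 2's definition that would be unnecessary, which suggests that the narrow definition is meant as the working one.
3. Fieldworkers record AEs (8.2, 8.4, Table 3), and the site investigator assesses seriousness, causality and expectedness of those AEs (8.4, Table 3). An event outside the AE definition has no stated entry to these steps.

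For non-serious events the literal result is therefore that they are not recorded. For serious events there are two readings. The serious definition in Table 2 is unrestricted, and 8.3 says that both AEs and SAEs are asked about and recorded. Yet 8.3 and 8.4 attach the seriousness assessment to an event already called an AE. The text does not settle which reading applies.

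Falling back on Table 2 alone would not resolve everything. Its AE definition refers to participants who received the intervention, whereas 8.2 expressly covers all groups, including the waiting list. Section 8.2 is thus narrower in type of event but wider in who is covered.

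**The case against.** The case against a stronger reading is good, and most of it stands.

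- **Serious cases.** A reader might infer that a man with known diabetes admitted with low blood sugar, or one with known depression who becomes suicidal, would be lost altogether. The documents do not support that. The first meets the hospitalisation criterion in Table 2. The second can meet the medically significant criterion, and 8.8 separately covers concerns raised at any contact and by text screening. Only the ambiguity described above remains.
- **Reporting to the ethics committee.** A reader might infer that the 15-day report is compromised. Section 8.6 reserves that report for serious events that are related and unexpected. Anything on the 8.4 list is expected by definition and would not take that route however 8.2 were worded. For listed serious events, the relevant output is the periodic summary of related SAEs.
- **Size.** A reader might take the Feasibility Study co-morbidity rates (87% of GP recruits, 44% of community recruits), average them at a 50:50 split to 65.5%, and apply that to 585 men to reach about 383. That counts men with a condition at entry, not events lost. The split is also stated to be flexible, and bowel changes or muscle pain can occur in men with no co-morbidity. It does not measure this problem.
- **Legitimate choice.** A low-risk self-management trial may use a narrow AE definition, CRF guidance is not shown, and 8.2 applies to all groups alike. That is fair: variation between centres is a possibility and has not been shown, and the wording of 8.2 does not itself favour an arm. It does not remove the conflict, because the expectedness list shows that the protocol intends these events to be assessed.

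**Conclusion.** The point holds as an internal contradiction with a limited consequence. Section 8.2 cannot be reconciled with Table 2 or with the 8.4 list as written. Read literally, it omits non-serious symptoms and non-serious worsening of known conditions from the 12-month adverse event outcome and from PMG and TSC review, and it leaves the route for serious cases unclear.

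It would go too far to say that such events definitely will not be recorded or reported: the protocol gives conflicting instructions, and the broader Table 2 text is still there. The exclusion is also partial, since injuries and new diagnoses on the list are captured.

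No event count can be derived from the protocol. The primary estimate, alpha and sample size are unaffected. The conclusion assumes that Fieldworkers apply 8.2 as worded and that no CRF guidance already overrides it. This should be fixed, but it does not threaten the trial's main conclusions.

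**What to change.** Reconcile 8.1, 8.2 and 8.4 in one wording change.

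1. Widen the first bullet of 8.2 to: *any injury, any newly diagnosed health condition, any worsening of a pre-existing condition, or any event of a type listed under Assessment of Expectedness*, keeping the present text that it applies in every group and whether or not related.
2. Add: *any event meeting a seriousness criterion in Table 2 is recordable, subject to the exclusions in the third bullet of this section*. The cross-reference must cover the whole of that bullet (hospitalisation planned before randomisation, routine elective hospitalisation, and complications during either). Otherwise the new sentence would contradict it.
3. Carry the same wording into the CRF guidance for all three centres. If the change is made after follow-up contacts have begun, record its date and say in the report which definition applied to which contacts.

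The cost is somewhat more AE entries for Fieldworkers and site investigators to process. One consequence should be settled in advance: the list names changes in diabetic medication without qualification, so a reduction following weight loss would become an entry, and the protocol should state how such entries are to be presented. No additional contacts are needed, because 8.3 already provides for open-ended questioning at each visit.

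### Section 8.2 bars recording of any complication during an elective admission, which contradicts the all-deaths rule in the next bullet and conflicts with the Table 2 seriousness criteria

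*Protocol*

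**What the plan says.** Table 2 (Section 8.1) gives the general seriousness criteria: death, a threat to life, an event that "requires inpatient hospitalisation or prolongation of existing hospitalisation", lasting disability, or any other event that the investigator regards as medically significant.

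Section 8.2 then sets four working rules for this trial.

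- First bullet: "An adverse event is defined as any injury or newly diagnosed health condition" arising during participation, in any group, related or not.
- Second bullet: recording runs from consent to the end of the 24-month follow-up.
- Third bullet: "Hospitalisations for treatment planned prior to randomisation and routine hospitalisation for elective treatment" count as neither AE nor SAE. The bullet ends: "Complications occurring during such hospitalisation will also not be considered, recorded or reported as an AE or an SAE".
- Fourth bullet: "Any death that occurs during the trial is very unlikely to be related, but all deaths will be documented as AE and relatedness determined".

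Under Section 8.4 the site's principal investigator judges seriousness (against Table 2), causality and expectedness. Causality expressly covers the man's own attempt to lose weight. Events judged related are then sorted into expected and unexpected; the expected list includes "Gall stones, newly manifest or worsening of known symptoms" and cardiovascular events. Section 8.5 asks for medical review of serious events judged unrelated, or related and unexpected. Section 8.6 sends summaries of all related SAEs to the ethics committee, the funder and the Trial Steering Committee (TSC).

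**The concern.** The third bullet has two limbs, and only the first is bounded in time. The second covers any routine elective admission, including one for a problem that arose or worsened after randomisation. The complications sentence then applies to both limbs and makes no distinction by outcome, severity or cause.

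The filter works before anyone judges seriousness or relatedness. An event it removes is never assessed, so no one can find that it was related. Whether a serious complication counts then depends on how the admission was booked, not on what happened to the man.

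Little elsewhere in the protocol would recover such an event. Staff have no access to hospital or GP records and depend on the participant's account (Section 8.3). Linkage to routine records will not take place during the study (Section 6.7). There is no separate data monitoring committee, and the TSC fills that role (Sections 2.1, 8.5 and 9.5).

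**Working it through.** No arithmetic applies: the point turns on the wording of the recording rules, and nothing in it touches sample size, power or alpha. The check takes four cases through the rules.

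1. **Death from a complication of an elective admission.** The third bullet of Section 8.2 says the complication is not recorded. The fourth says every death is recorded and its relatedness determined. Neither bullet makes an exception for the other, and nothing states an order of precedence. These are two operational rules of equal rank in the same section, so this is a direct contradiction.

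2. **Non-fatal serious complication**, such as a myocardial infarction or a prolonged stay during an elective admission. It can meet Table 2 as life-threatening or as prolonged hospitalisation. If it is a new diagnosis, it also meets the first bullet's definition of an adverse event. The third bullet still excludes it, and no other bullet brings it back. It therefore does not reach the causality judgement in Section 8.4, the medical review in Section 8.5 or the reporting in Section 8.6.

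3. **Condition newly diagnosed after randomisation and treated by elective admission**, such as gall stones. The third bullet excludes the admission and its complications, not the condition. The diagnosis remains an adverse event under the first bullet and may still be graded serious under Table 2's medical-significance criterion. What cannot be used is the admission as the ground for seriousness. If no other criterion is applied, the event is recorded as non-serious and goes to the project management group and the TSC as such, outside the related-SAE summaries.

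4. **The admission or operation itself, planned before randomisation.** No rule in the protocol asks for it to be captured, and excluding it conflicts with nothing.

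Case 1 is a contradiction, case 2 a conflict with the seriousness criteria, case 3 a partial loss, and case 4 no defect.

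**The case against.** The strongest reply has four parts.

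*Deaths are covered.* The fourth bullet follows the exclusion directly and is specific and unqualified, so it is naturally read as governing deaths. A reader might infer from the third bullet that deaths are removed from the record; the document does not support that. It supports only that a death in an excluded admission falls under two rules with no stated precedence. One clause would settle it, but the clause is absent, and staff who apply the third bullet as written would not record the complication.

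*The expected-event list creates no duty to capture.* This is correct. A reader might infer that the list obliges the trial to record surgery linked to weight loss. It does not: it names conditions rather than operations, and it only classifies events already judged related. Nor is a new gall stone diagnosis lost, as case 3 shows.

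*Section 8.2 may narrow Table 2.* Table 2 sits under standard definitions and Section 8.2 under definitions for this study, and a trial may narrow general criteria. That has some force: the clash with Table 2 is weaker than the clash between the two bullets. But Section 8.4 sends the assessor back to Table 2 without mentioning the exclusion, and the narrowing removes serious events before relatedness is considered.

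*The setting is low risk.* The protocol describes the intervention as very low risk (Section 3.2) and reports no safety concerns in the Feasibility Study (Section 9.5). Most extra events would probably be unrelated. This limits the likely number, but it does not explain why relatedness should go unassessed.

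**Conclusion.** The point holds in a limited form. The complications sentence in Section 8.2 has no exception for fatal, life-threatening or related events, and its elective limb has no time limit. It contradicts the all-deaths bullet for deaths that arise as complications of excluded admissions. It conflicts with Table 2 for non-fatal serious complications and keeps them from being assessed or reported. For a new condition treated electively, the loss is confined to the admission-based seriousness grading and any complications.

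The size cannot be given as a number, because the protocol states no rate of elective admission or of complications. By rule, no complication within an excluded admission is captured. This applies in all three groups, across the planned 585 men, for as long as events are collected; collection to 24 months itself depends on the TSC's decision to continue. That describes the rule and is not an estimate of harms missed. The conclusion assumes that staff apply the third bullet as written. If unshown CRF guidance already gives precedence to the deaths rule, case 1 is resolved in practice, though the protocol text would still need to say so.

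**What to change.** Reconcile Section 8.2 with Table 2 by rewording the third bullet:

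- limit the exclusion to the admission itself, where the treatment was planned before randomisation;
- replace the complications sentence so that any complication meeting Table 2 is recorded and assessed for seriousness, relatedness and expectedness under Section 8.4;
- state that the rule on deaths prevails over the exclusion.

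Align the CRF guidance for Fieldworkers with the new wording. The cost is one bullet, the matching guidance and a few more events to record and assess, most of them likely to be judged unrelated. No extra resources or new data sources are needed, and the sample size and analysis are unaffected.

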### **8.3. Detecting AEs and SAEs**

At each contact with a participant (3, 6, 12 and 24M), the Fieldworker will ask about the occurrence of AEs/SAEs. Open-ended and non-leading verbal questioning of the participant will be used to enquire about AE/SAE occurrence. If any AE is likely to meet the criteria for an SAE, as much detail as possible about the event will be sought from the participant. This a community-based study, and the Fieldworker and PI will not have access to hospital or GP medical records, so the only source of information about the event is likely to be from the participant themselves. AEs/SAEs will be recorded, evaluated, reviewed and reported as described below.

In addition, the research team may be alerted to a possible AE/SAE via screening of text message responses (see Section 8.8 on Safeguarding), or by direct contact with the trial office. If the AE/SAE is confirmed, this will be recorded, evaluated, reviewed and reported as described below.

